### **3.2 Endpoints**

#### Primary endpoint

The primary endpoint is LVEF at 6 months postoperatively, measured by MRI at rest. Cardiac MRI is established as the gold standard for determination of LV function (LVEF and LV volumes).

#### Secondary endpoints

1. Change in LVEF at 6 months post-OP compared with preoperatively (screening) and early postoperatively (discharge) as assessed by MRI and echocardiography.
2. Change in LV dimensions (left ventricular end systolic dimension [LVESD], left ventricular end diastolic dimension [LVEDD]) at 6 month post-OP compared with preoperatively (screening) and early postoperatively (discharge) as assessed by echocardiography.
3. Change in physical exercise capacity determined by 6 minute walk test at 6 months post-OP compared with preoperatively (screening) and early postoperatively (discharge).
4. Change in NYHA and CCS class at 6 months post-OP compared with preoperatively (screening) and early postoperatively (discharge).
5. MACE (cardiac death, myocardial infarction, secondary intervention/reoperation, ventricular arrhythmia).
6. QoL-score at 6 months post-OP compared with preoperatively (screening) and 3 months post-OP (telephone).

### **3.3 Justification of the Study Design**

The study design results from our experience with phase I and phase II studies in Rostock. CD133+ positive bone-marrow stem cells were isolated from the patients own bone marrow (iliac crest puncture) and prepared according to GMP standards. Small volume preparations of 5 mL were found safe for intramyocardial application using 0.2–0.3 mL volume per injection. The distribution of injection-sites was found best using one injection per square cm and 26 gauge injection needles. The injections were placed in the

borderline tissue around patients' heart infarction, so that 10-15 injections are needed to circle around the infarction area.

The main limitation of the previous controlled study was the absence of a placebo-controlled randomized grouping to exclude influence of intramyocardial injection (saline) on myocardial function. No side-effects were found in the safety and efficacy trial. No rescue medication was necessary.

We have chosen the analysis of LVEF 6 months after CABG surgery by MRI as a primary endpoint to measure the effect on regeneration of the functionally impaired left ventricle after myocardial infarction. MRI is considered as gold standard for measurement of left ventricular function parameters. To exclude bias analysis will be done by a central MRI core-lab.

Additional secondary endpoints will underline the effects of the injection of autologously derived bone marrow stem cells with determination of physical exercise capacity, echocardiography, safety and QoL.

Former studies and experiments have shown that on average more than  $5 \times 10^6$  CD133+ bone marrow stem cells can be isolated from 200 mL bone marrow aspirate (Ghodsizad, 2004). In this trial  $0.5\text{--}5 \times 10^6$  CD133+ cells isolated from the harvested bone marrow will be administered. Cell yields lower than the expected  $0.5 \times 10^6$  but  $\geq 0.1 \times 10^6$  will be documented by the cell preparation team (Team A) and the information forwarded to the Statistician but not to the physician and the patient. These patients will be regarded as drop-outs but will be followed-up similar to the intend-to-treat population and evaluated separately.

Cell yields lower than  $0.1 \times 10^6$  will be documented and the product will not be released by the Team A. The patient will be dropped out of the study and the treating physician and Statistician will be informed. These patients will not be followed-up. In case the over-all drop-out rate exceeds the assumed 15% those patients that dropped-out post-hoc because of insufficient cell counts may be replaced.

## 4 STUDY POPULATION

The study population will consist of patients with coronary artery disease after myocardial infarction with an indication for CABG surgery. Patients must be able to provide written consent and meet all the inclusion criteria and none of the exclusion criteria.

### 4.1 Inclusion Criteria

Patients will be entered into this study only if they meet all of the following criteria:

1. Coronary artery disease after myocardial infarction with indication for CABG surgery
2. Currently reduced global LVEF assessed at site by cardiac MRI at rest ( $25\% \leq \text{LVEF} \leq 50\%$ )
3. Presence of a localized akinetic/hypokinetic/hypoperfused area of LV myocardium for defining the target area
4. Informed consent of the patient
5.  $18 \text{ years} \leq \text{Age} < 80 \text{ years}$
6. Are not pregnant and do not plan to become pregnant during the study. Females with childbearing potential must provide a negative pregnancy test within 1-7 days before OP and must be using oral or injectable contraception (non-childbearing potential is defined as post-menopausal for at least 1 year or surgical sterilization or hysterectomy at least 3 months before study start).

### 4.2 Exclusion Criteria

Patients will be entered into this study only if they meet none of the following criteria:

1. Emergency operation
2. Presence of any moderate-severe valvular heart disease requiring concomitant valve replacement or reconstruction
3. Medical History of recent resuscitation in combination with ventricular arrhythmia classified by LOWN  $\geq$  class II
4. Acute myocardial infarction within last 2 weeks
5. Debilitating other disease: Degenerative neurologic disorders, psychiatric disease, terminal renal failure requiring dialysis, previous organ transplantation, active malignant neoplasia, or any other serious medical condition that, in the opinion of the Investigator is likely to alter the patient's course of recovery or the evaluation of the study medication's safety
6. Impaired ability to comprehend the study information
7. Absence of written informed consent
8. Treatment with any investigational drug within the previous 30 days
9. Apparent infection (c-reactive protein [CRP]  $\geq 20 \text{ mg/L}$ , fever  $\geq 38.5^\circ \text{C}$ )
10. Contraindication for MRI scan
11. Immune compromise including Anti HIV 1/2, HBsAg, Anti-HBc-IgG, Anti HCV, Treponema pallidum
12. Pregnant or breast feeding
13. Childbearing potential with unreliable birth control methods
14. Have previously been enrolled in this study, respectively phase I and phase II

15. Known hypersensitivity or sensitization against murine products and human-anti-mouse-antibody-titer  $\geq 1:1000$
16. Contraindication to bone marrow aspiration
17. Known hypersensitivity against iron dextrane

### 4.3 Patient Withdrawal and Replacement

Patients may withdraw from the study at any time without penalty and for any reason without prejudice to his or her future medical care. All patients will be closely monitored by their individual cardiologist and general practitioner and treated as appropriate, according to the guidelines issued by the national and international cardiology organizations that relate to patients with coronary artery disease and patients with congestive heart failure. The Investigators reserve the right to conduct additional follow-up examinations.

Patients must be withdrawn under the following circumstances:

- The patient withdraws consent;
- Pregnancy. If patients are to withdraw due to pregnancy, they should be followed-up until the outcome for the mother and fetus are known.
- If serious clinical events (e.g., emergency surgery, myocardial infarction, stroke, fever  $\geq 38.5^{\circ}\text{C}$ ) occur between recruitment and planned surgery.

Patients may be required to withdraw after discussion with the Sponsor and/or Investigator for the following reasons:

- Adverse event(s);
- At the discretion of the Investigator;
- Violation of eligibility criteria;
- Deviation from the treatment plan specified in the protocol (e.g., incorrect administration of the study drug, failure to attend study visits).

In all cases, the reason(s) for withdrawal, and the primary reason, will be recorded on the case report form (CRF). If a patient is prematurely withdrawn from the study for any reason, the Investigator will make every effort to perform the evaluations described for the Early Termination Visit (see Section 7.2.6.2).

An excessive withdrawal of patients can render the study uninterpretable. Therefore unnecessary withdrawal of patients should be avoided. In case of withdrawal, all efforts should be made to complete and report the observation and justification of withdrawal in as much detail as possible. Withdrawn patients that dropped-out of the study because of SAE will not be replaced. However, patients who are not able to reach the primary endpoint because of their body size/weight may be replaced.

Patients from both groups, who either received Placebo or CD133+ cells may be excluded post-hoc from the study because of insufficient CD133+ cell counts ( $<0.5$  Mio but  $\geq 0.1$  Mio). In case the drop-out rate exceeds the assumed rate of 15% these patients may be replaced. Furthermore, patients who were randomized but did terminate the study before treatment may be replaced.

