### **5.2 Administration**

Patients randomized to the active treatment group will be given 5 mL CD133+ cells, saline and serum suspension intramyocardially during CABG surgery (see Section 5.10 for further details on CABG surgery).

Patients randomized to placebo treatment will be given 5 mL saline plus serum solution intramyocardially during CABG surgery

For both treatment groups, the treatments will be administered intramyocardially in the infarction border zone (penumbra) during the cardiac surgical procedure. The procedure will be performed with extracorporeal circulatory support, aortic cross clamping and cardiac arrest induced by cardioplegia according to the center standards. The treatments will be administered before cross clamp release.

A series of fifteen individual injections (1 mL syringes, 26 Gauge needle) of 0.3 mL aliquots (in total 5 mL, including up to 0.5 mL rest in syringes) will be applied within 3 minutes in the region of interest (infarction border zone) at the end of bypass surgery (before the release of aortic cross clamp). No more than one injection per square centimeter should be injected. For documentation of injection sites see Figure 5.

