## **5.6 Compliance**

The study treatment will be administered by the Investigator therefore patient compliance with study treatment will not be monitored.

Patients that are non-compliant with the study protocol such as non-attendance at study visits or refusal to undergo certain assessments may be candidates for patient withdrawal (see Section 4.3).

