### 8.1.3 *Analysis Populations*

Two different sets of patients will be defined to perform analyses. A “Full Analysis Set” (FAS) following the principle of intent-to-treat (ITT) will include every patient as randomized and compare the patients according to the group to which they were randomly allocated, regardless of patients' compliance, or withdrawal from the study. It is the most cautious approach and so minimizes type 1 error, helps preserve prognostic balance in the study arms and allows for the greatest generalizability.

Secondly, an analysis of all per protocol treated patients will be performed. The “Per Protocol Set” (PPS) is a subset of the FAS patients who are compliant with the study protocol. The PPS sample will consist of all subjects from the FAS group without any major protocol violation.

First and foremost, confirmatory analyses on primary efficacy variable will be performed on the FAS patients but a secondary analysis will also be performed based upon the Per Protocol Set, to assess the sensitivity of the analysis to the choice of analysis population. The ITT analysis will be considered as the primary one.

Patients who received the cellular product or Placebo but dropped-out post-hoc because of cell count insufficiency will be evaluated separately.

The safety population will comprise all patients randomized into the study, in which each patient's treatment is as taken on the study. Safety evaluations will be performed on the safety population.

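### Sections 4.3 and 5.6 allow injected patients to be withdrawn from follow-up, not only from treatment, so month-6 LVEF can go missing for outcome-related reasons; the size and direction of any bias are unknown

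*Protocol*

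**What the plan says.** Section 4.3 has two lists. In the mandatory list, the ground for serious clinical events is confined to the interval between recruitment and planned surgery. The second list is discretionary: "Patients may be required to withdraw after discussion with the Sponsor and/or Investigator for the following reasons". Its grounds are adverse events, the investigator's discretion, eligibility violation, and "Deviation from the treatment plan specified in the protocol (e.g., incorrect administration of the study drug, failure to attend study visits"). It has no time limit. Section 5.6 adds: "Patients that are non-compliant with the study protocol such as non-attendance at study visits or refusal to undergo certain assessments may be candidates for patient". What they may be candidates for is withdrawal, and the sentence refers back to 4.3. Section 7.2.6.2 repeats the discretionary grounds as reasons on the combined 6-month/early-termination visit.

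Treatment is given once. Under section 5.2 the injections "will be applied within 3 minutes in the region of interest (infarction border zone) at the end of bypass surgery". The outcome comes much later: "The primary endpoint is LVEF at 6 months postoperatively, measured by MRI at rest".

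Section 8.1.3 says the full analysis set will "compare the patients according to the group to which they were randomly allocated, regardless of patients' compliance, or withdrawal from the study". Section 8.2 states that missing values are not replaced. Section 8.5 analyses 6-month LVEF by ANCOVA with baseline LVEF and site.

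Section 4.3 also provides: "If a patient is prematurely withdrawn from the study for any reason, the Investigator will make every effort to perform the evaluations described". These evaluations are those of the early-termination visit. It also asks that unnecessary withdrawal be avoided. For withdrawn patients, section 6.3.1.3.2 sets SAE reporting at up to 30 days after injection.

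**The concern.** Once the injections are given, no study treatment remains to be stopped. Withdrawal after that point ends scheduled observation, not exposure. The discretionary list does not draw this distinction, and two of its examples, incorrect administration and missed follow-up visits, point to events at or after injection.

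The primary objective concerns the effect in the patients randomised, and section 8.1.3 promises that comparison "regardless of patients' compliance, or withdrawal from the study". If a patient is withdrawn because of an adverse event and has no month-6 scan, the analysis can honour that promise only in name. Adverse events and investigator discretion are the clearest outcome-related grounds. Incorrect administration is less directly so. An eligibility violation is a baseline fact, and a missed visit is already missing data, to which withdrawal adds only later missingness.

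There is also a safety side: the 30-day limit in section 6.3.1.3.2 shortens the reporting window for new SAEs in the patients whose course may be of most interest.

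**Working it through.** **1. How a withdrawn patient leaves the comparison.**
- Section 4.3: an injected patient may be withdrawn from the study.
- Section 8.1.3: the patient remains in the full analysis set.
- Sections 4.3 and 7.2.6.2: an early-termination visit, which includes cardiac MRI, is attempted. The protocol does not say that an MRI taken before month 6 serves as the 6-month value.
- Sections 8.2 and 8.5: if there is no 6-month LVEF, nothing replaces it, and the ANCOVA has no outcome for that patient.

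**2. The plan's own sample size.** Inputs from section 8.7: difference 4.5, SD 7.5, two-sided 5%, power 90%, drop-out 15%. With the noncentral t, power is 90.3% at 60 per group and 89.8% at 59, so 60 is the minimum. Then 60 / (1 - 0.15) = 70.6, rounded up to 71 per group, 142 in total. The plan's figure reproduces. The 15% allowance protects precision; it does not remove selection bias.

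**3. Form of the bias.** Let w be the share of an arm removed, D the LVEF deficit of removed versus retained patients that baseline LVEF and site do not explain, and R the retained mean. The all-randomised mean is (1 - w)R + w(R - D) = R - wD, so the retained mean exceeds it by wD. With 1 for the cell arm and 0 for placebo:

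bias in the difference = w1·D1 - w0·D0.

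The protocol gives no w for these grounds and no D. All values below are assumptions.

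| w1 | D1 | w0 | D0 | Bias (LVEF points) |
|---|---|---|---|---|
| 15% | 7.5 | 15% | 7.5 | 0 |
| 15% | 7.5 | 15% | 4.5 | 1.125 - 0.675 = +0.45 |
| 20% | 7.5 | 10% | 7.5 | 1.50 - 0.75 = +0.75 |
| 10% | 7.5 | 20% | 7.5 | 0.75 - 1.50 = -0.75 |

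If removals occur in one arm only, with w from 5% to 15% and D from 3.75 to 11.25 (0.5 to 1.5 SD), the absolute shift runs from 0.05 × 3.75 = 0.19 to 0.15 × 11.25 = 1.69 points. The sign depends on the arm.

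**4. What a shift would do to the error rate.** This is a single-stage t-test illustration that ignores the two-stage combination test of section 8.8. Take a net shift of +0.75, SD 7.5 and 60 per arm:
- standard error = 7.5 × √(2/60) = 1.369
- noncentrality = 0.75 / 1.369 = 0.548
- critical value (df 118, one-sided 2.5%) = 1.980
- P(T > 1.980) = 7.8%, against 2.5% with no shift

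With a shift of -0.75 the same upper-tail probability is 0.6%.

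**The case against.** The strongest case against is substantial, and most of it stands as a limit on the size of the point.

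- **The rule is permissive.** It says may, requires discussion, and sits beside a request to avoid unnecessary withdrawal. The number affected is therefore unknown and could be small. The request still leaves every listed ground in force.
- **Nobody is removed from the analysis set.** A reader might infer that 4.3 lets the sponsor take patients out of the all-randomised set. Section 8.1.3 says the opposite; patients are lost only through a missing month-6 value.
- **An MRI is attempted at early termination.** That is a real mitigation, and the SAP may say how the scan is used. But it is best-effort and may be early, and no SAP can recover a month-6 scan that was never taken.
- **Blinding.** Patients, surgeons and assessors are blinded and both arms are injected, so administration errors and missed visits should be similar across arms. A reader might infer that the bias favours the cells. The documents do not support that: direction depends on both arms. The 7.8% figure also requires cells that alter withdrawal while leaving mean LVEF unchanged. Blinding does not prevent imbalance if the cells themselves affect adverse events, and section 1.3 lists ventricular arrhythmia and deterioration of heart function as potential risks.
- **The 15% allowance.** It should not be read as the share removed on these grounds. The drop-outs the plan discusses include low cell yield, and deaths and patients' own withdrawals also cost scans.
- **Withdrawal can serve a purpose.** A reader might infer that it only ends data collection. That goes too far: participation includes stress-perfusion MRI (6.1.5) and a walk test barred in severe rhythm disturbance (6.1.7), and existing adverse events are still followed (6.3.1.4). This supports omitting a procedure, which does not require ending all follow-up.

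**Conclusion.** The point holds as a cheap and worthwhile improvement to the protocol. Sections 4.3 and 5.6 do not separate withdrawal from treatment from withdrawal from follow-up. Combined with section 8.2, this allows outcome-related loss of the primary endpoint that section 8.1.3 is meant to guard against, and it shortens SAE reporting in withdrawn patients.

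No bias has been demonstrated. Its size and direction cannot be derived from the protocol, and it is zero when w·D is the same in both arms. The shifts in the working, and the rise in one-sided error from 2.5% to about 7.8% at +0.75 points, rest entirely on assumed removal shares and deficits. They show what could be at stake, not what is expected.

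**What to change.** In sections 4.3 and 5.6, distinguish withdrawal from treatment from withdrawal from follow-up. State that, after injection, the discretionary grounds are recorded as adverse events or protocol deviations, with deviations bearing on the per-protocol set only. Consenting patients then remain in follow-up to the month-6 MRI and the scheduled safety assessments. An individual study procedure may still be omitted where the investigator judges it unsafe.

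The new wording must be reconciled with two existing rules that also require withdrawal: pregnancy in section 4.3, and unblinding of the patient, investigator or assessing staff in section 5.4. A blanket statement that only consent withdrawal or death ends follow-up would contradict both.

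The protocol has a precedent: section 3.3 keeps patients with low but releasable cell counts under follow-up although it calls them drop-outs. The month-6 visit is already scheduled for every patient, and the planned 142 does not change. The cost is the amended wording, some extra effort to retain or recall patients, and less discretion to end participation.

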### 4.4 Planned Sample Size and Number of Study Centers

It is planned to recruit 142 patients at seven centers in Germany for this study. Each center should enroll between 20 and 80 patients. See Section 8.7 for a discussion of sample size.

#### 4.5 Patient Identification and Randomization

Upon enrollment, each patient will receive a four-digit **patient number** consisting of (x-yza). The 1st digit assigned x, indicates the study site (–see List of trial personnel), the 2nd, 3rd and 4th digit assigned, yza, indicates the individual patient. Enrolled patients who drop out of the study before randomization will retain their patient number.

Randomization to study treatment will occur at Assessment Ia (cell-preparation) after all screening procedures have been performed, eligibility for the study confirmed and after bone-marrow aspiration. The randomization will be attributed by Team A (cell processing team). Each randomized patient will receive a four-digit **randomization number** (x-yza). The 1st digit assigned, x, indicates the study site (–see List of trial personnel), the 2nd and 3rd and 4th digit assigned, yza, indicates the individual patient.

Randomized patients who terminate their study participation for any reason, regardless of whether study intervention was taken or not, will retain their randomization number. The randomization code will be assigned using sealed envelopes provided to the Team A for each study center.

Patients will be randomized on a 1:1 basis to receive CD133+ cells or placebo.

The randomization procedure will be stratified by study site and a sequence of randomization numbers will be assigned to the bone-marrow isolation laboratory (Team A) preparing for the study centers. As randomization procedure the Permuted Block Design within strata will be used (Rosenberger and Lachin, 2002). The block size within each stratum will be randomly selected. The size of the randomization blocks as well as seed numbers will be documented but will not be disclosed to the study centers to avoid predictability of treatment. The study treatment will be randomly assigned to the randomization numbers in advance according to the randomization list held by the Biostatistician.

The randomization envelopes are numbered in an ascending order. If a patient is going to be randomized a member of Team A opens the envelope with the lowest number among all unused sealed envelopes available for this center. According to the information randomization will be carried out and CD133+ cell or placebo product will be produced for the current patient.

The randomization code will be stored by the Statistician. Only the members of Team A will have access to the randomization code. All members will sign an agreement, stating that the randomization code will be kept confidential and no person outside the trial Team A will have access to the code.

At each site sealed emergency envelopes will be stored at a secure place containing the randomization code. In case of an emergency which requires knowledge of treatment the treatment code for an individual patient can be revealed to a member of Team B (treatment team) by opening the sealed envelope. See Section 5.4 for details of breaking the blind.

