## **5 STUDY TREATMENT**

### **5.1 Identity**

All patients enrolled in the study will undergo bone marrow aspiration (150-200 mL) and withdrawal of 20 mL blood one to two days before CABG surgery at Assessment Ia.

As there is only autologous application of the stem cells each patient is his own donor. Herewith the inclusion and exclusion criteria of the study population and the assessments describe the selection and testing of the donors.

For all patients CD133+ cells will be selected from the bone marrow aspirate. For patients randomized to the active treatment group the cells will be suspended in physiological saline + 10% autologous serum. For the patients of the control group, the CD133+ cells will be stored at the manufacturer. See Section 5.8 for further details of bone marrow aspiration and Section 5.9 for further details of CD133+ cell and placebo preparation and treatment.

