#### ***5.9.3 Practices with final formulation of CD133+ Cell Product which do not fulfill the release requirements***

Final formulations which do not fulfill the release requirements will not be used in the study. The patient will be dropped out of the study and the treating physician and Statistician will be informed.

The Statistician will inform the Safety Monitoring Board, if the drop-out rate exceeds the calculated limit (see also 3.3).

In accordance with the patient's consent the cells which are not administered will either be used for research or will be destroyed.

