#### 8.1.2 *Protocol Deviations*

Every deviation from the trial protocol must be specified and documented in writing separately for each patient. The Investigator has to report the protocol deviation to the sponsor. The Investigator must consult with the monitor and discuss the type and extent of deviation as well as the possible consequences for further participation of the patient in the study. If the evaluability of a patient is questionable the national coordinating Investigator, the trial site principal Investigator and the biometrician will be consulted. Major violations leading to exclusion from the PPS (Per Protocol Set) will be defined during the blind review meeting and in agreement with the Sponsor after data cleaning but before database closure and before breaking the randomization code.

One of the following surgical complications will lead to post-hoc exclusion from the study:

- Perioperative cerebral ischemic insult with persisting relevant neurologic deficit
- Deep sternal wound infection
- Rare surgical complications (i.e. respiratory failure with need for prolonged mechanical ventilation, intestinal infarction, several acute pancreatitis, chronic chylothorax, aortic dissection, peripheral ischemia requiring surgery)

Patients with one or more major protocol violations will be excluded from PPS group leading to the exclusion of all efficacy data from the PPS analysis, if one of the following criteria is fulfilled:

- Patients without measurement after 6 months for LVEF
- Violation of inclusion or exclusion criteria.

Number of patients with protocol deviations during the study and listings describing the deviations will be provided. Patients that are not attendant at study visits or refuse to undergo certain assessments are non-compliant with the study protocol. Listings and frequency tables of those patients will be provided.

The insufficiency of CD133+ cell counts (less than  $0.5 \times 10^6$  but  $\geq 0.1 \times 10^6$ ) will lead to post-hoc exclusion from the study but patients will be followed-up similar to the intend-to-treat population.

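### Randomisation does not wait for cell yield or product release, and the drop-out rules that follow conflict with the all-randomised primary analysis set

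*Protocol*

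**What the plan says.** **Timing of allocation.** Section 4.5 states: "Randomization to study treatment will occur at Assessment Ia (cell-preparation) after all screening procedures have been performed". Confirmed eligibility and completed aspiration are the other conditions. It continues: "If a patient is going to be randomized a member of Team A opens the envelope with the lowest number among all unused sealed envelopes". The envelope then determines whether a "cell or placebo product will be produced for the current patient". Section 7.2.2 and Table 2 both list randomisation ahead of cell/placebo preparation. None of these places makes randomisation depend on a count or a release test.

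**Cells are isolated in both arms.** Section 5.1 says of all patients that CD133+ "cells will be selected from the bone marrow aspirate". Control-arm cells are stored by the manufacturer.

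**Losses after randomisation.**
- Below 0.1 million cells (section 3.3): the product is not released, the patient leaves the study, and the treating physician and statistician are told. "These patients will not be followed-up".
- Release failure (section 5.9.3, whose title names the CD133+ product): "Final formulations which do not fulfill the release requirements will not be used in the study". The patient is dropped and the treating physician is informed.
- From 0.1 to under 0.5 million cells: section 3.3 counts these patients as drop-outs. Section 4.3 says that patients of both groups may be excluded after treatment. Section 8.1.2 is firmer: the low count "will lead to post-hoc exclusion from the study but patients will be followed-up similar to the intend-to-treat population". Section 8.1.3 adds that treated patients who "dropped-out post-hoc because of cell count insufficiency will be evaluated separately".
- Replacement: sections 3.3 and 4.3 allow low-count patients to be replaced if drop-out exceeds 15%. Section 4.3 also allows replacement of randomised patients who leave before treatment.

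**Primary analysis set.** Section 8.1.3 defines the FAS as all randomised patients in their allocated group, whatever their compliance or withdrawal, and makes it primary. Section 8.2 says that missing values are not replaced.

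**The concern.** CD133+ yield is a property of the patient's marrow and is obtainable in both arms without knowing the allocation. The plan uses it after randomisation, to remove patients, when it could be used before.

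Three things are at stake:
- The confirmatory comparison is meant to include everyone randomised. Patients below 0.1 million cells can contribute no 6-month LVEF, and the place of the 0.1 to under 0.5 million group in the FAS is unclear.
- If release failure occurs only where a cell product is made, active patients are lost for a reason that has no counterpart under placebo.
- In that case, telling the treating physician that a product was not released also reveals the allocation. The laboratory team that documents yield and withholds release knows the allocation as well (sections 3.3 and 5.4).

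**Working it through.** **1. The plan's own sample size.** Inputs from section 8.7: difference 4.5, SD 7.5, two-sided alpha 0.05, power 90%, 15% drop-out.
- Non-centrality with n = 60 per arm: √60 × (4.5/7.5)/√2 = 3.29. With 118 degrees of freedom, power is 90.3%; n = 59 gives 89.8%. So 60 per arm is reproduced.
- 60/0.85 = 70.6, rounded up to 71 per arm, or 142 in total. The drop-out allowance is 142 − 120 = 22.

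The sample size is correct as stated.

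**2. What happens to each kind of randomised patient.**

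| Situation | Treated? | Followed? | Arm | Place in FAS |
|---|---|---|---|---|
| Under 0.1 million | No | No (3.3) | Not stated | In by 8.1.3, but no outcome |
| Other release failure | No | Not stated (5.9.3) | Criteria written for cell product only (5.9.1) | In by 8.1.3, outcome uncertain |
| 0.1 to under 0.5 million | Yes | Yes (3.3, 8.1.2) | Both (4.3) | In by the FAS definition; excluded from the study by 8.1.2 |

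The third row shows that allocation is not conditional on yield, whatever the exact moment of envelope opening: these patients have already received cells or placebo when they are excluded.

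**3. Could a loss be one-armed?** Section 5.9.1 sets count, depletion (2.5 log) and viability (80%) limits for the CD133+ product. Section 5.9.2 describes placebo as saline with autologous serum, and no release limits are given for it. On that wording, a viability or depletion failure can remove only an active patient. The protocol does not say so, nor whether stored control-arm cells are tested.

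**4. Effect on power.** No failure rate is given, so a range is assumed: a share r of active patients is lost on top of the planned 15% in both arms. Evaluable active patients = 71 × 0.85 × (1 − r); evaluable controls = 71 × 0.85 = 60.4.

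| r (assumed) | Active | Control | Power |
|---|---|---|---|
| 2% | 59.1 | 60.4 | 90.2% |
| 5% | 57.3 | 60.4 | 89.7% |
| 10% | 54.3 | 60.4 | 88.9% |
| 15% | 51.3 | 60.4 | 87.9% |

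**5. Effect on the estimate.** Suppose the lost active patients would have had a mean LVEF k points below those kept (k assumed). The active mean is then too high by r × k.

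| r | k = 2 | k = 4.5 | k = 7.5 |
|---|---|---|---|
| 2% | 0.04 | 0.09 | 0.15 |
| 5% | 0.10 | 0.23 | 0.38 |
| 10% | 0.20 | 0.45 | 0.75 |
| 15% | 0.30 | 0.68 | 1.13 |

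The planned difference is 4.5. If k is negative, the bias goes the other way.

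**The case against.** Several stronger readings are tempting, and the document does not support them.

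- **That the envelope is certainly opened before the count is known.** Section 4.5 places randomisation at the cell-preparation visit without fixing the moment, section 5.1 is compatible with selection coming first, and the manufacturing scheme (Figure 6) is not shown. Section 7.2.2 and Table 2 point to early opening, but they are visit checklists. What stands is that no result is required before allocation.
- **That envelope timing causes the loss at 0.1 to under 0.5 million cells.** It does not. These patients meet the release minimum and are treated on purpose in both arms. The exclusion rule causes the loss, and moving the envelope alone would not remove it.
- **That losses are known to be one-armed.** The 0.1 to under 0.5 million group is two-armed. Section 3.3 names no arm below 0.1 million. Only failure on viability or depletion points to the active arm, and only by inference.
- **That the primary analysis is no longer by intention to treat.** The FAS definition is sound, low-count patients are followed, and separate evaluation could mean an additional analysis. Only the group below 0.1 million plainly lacks follow-up. The rest is a conflict of wording.
- **That yield failures use up most of the drop-out allowance.** At assumed rates of 5%, 10% or 15% they would take 7, 14 or 21 of the 22. But section 3.3 expects more than 5 million cells on average from 200 mL, and the earlier studies' range in section 5.9.2 starts at 1.08 million, above 0.5 million. The specification was revised later, so low yields are possible, but nothing supports a particular rate.

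Blinded central reading of the MRI (sections 6.1.1 and 6.1.5) also limits what an unblinded physician could do to the primary endpoint.

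**Conclusion.** The point holds. Randomisation is not conditional on yield or release although cells are selected in every patient, and the rules for the resulting drop-outs conflict with a primary set of all randomised patients. For patients below 0.1 million cells the conflict is definite: they belong to the FAS but are not followed. For those at 0.1 to under 0.5 million, FAS membership is contradictory and needs one answer. A loss confined to the active arm, with the unblinding that would follow, is possible on the wording but not established.

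The size is modest and rests on assumed rates. Power stays between about 90% and 88% for an active-only loss of 2% to 15%. Bias is 0.1 to 0.75 LVEF points for a loss of 5% to 10% when the lost patients would have been 2 to 7.5 points worse. The reason to correct it is selection after randomisation, not sample size: outcomes of patients who were never followed cannot be recovered in the analysis.

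**What to change.** **Sections 4.5 and 7.2.2.** State that the envelope is opened only after CD133+ selection and after the in-process count, viability and depletion results have been recorded for every aspirate. Patients whose cells cannot be released are then not randomised.

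**Sections 3.3, 4.3, 5.9.3, 8.1.2 and 8.1.3.** State that every randomised patient, including low-count patients and late release failures, is followed to 6 months and kept in the FAS. Handle low count only in the PPS or a supplementary analysis. Delete the replacement of randomised patients for low count.

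**Thresholds.** The cell-count limits in sections 3.3, 4.3 and 5.9 must be reconciled by the sponsor. None is proposed here.

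**Cost.** A protocol amendment and a changed order of laboratory steps within the existing 72-hour limit; possibly the same in-process tests on control-arm cells, so it is not wholly free. A few failures from late results, such as sterility, will still come after randomisation. Marrow collections hardly change. If a share f of patients within the planned 15% loss is identified before allocation, the remaining drop-out is 1 − 0.85/(1 − f). For assumed f of 2%, 5%, 10% and 15%, 140, 136, 128 and 120 patients would be randomised to keep 60 evaluable per arm, from about 142 to 144 aspirations.
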